# Motivational Interviewing as a tool to enhance access to mental health treatment in adolescents with chronic medical conditions and need for psychological support (COACH-MI): study protocol for a clusterrandomised controlled trial

**DOI:** 10.1186/s13063-018-2997-5

**Published:** 2018-11-14

**Keywords:** Adolescents, adherence to medical treatment, anxiety, chronic condition, depression, motivational interviewing

## Abstract

**Background:**

This cluster-randomised monocentric controlled trial focuses on improving the uptake symptoms of mental health care in adolescents with chronic medical conditions who have been identified by screening to have depression or anxiety. The study aims to determine the efficacy of motivational interviewing (MI) delivered by trained physicians to increase 12- to 20-year-old adolescents’ utilisation of psychological health care for symptoms of anxiety or depression.

**Methods/design:**

In this single-centre approach, *n* = 1,000 adolescents will be screened (using PHQ-9 and GAD-7), and adolescents with results indicative of anxiety or depressive symptoms (*n* = 162) will be advised to seek psychological health care in clusters from treating physicians in specialised outpatient departments. Participants who screen positive will receive either two sessions of MI or treatment as usual (TAU; regarded as the typical daily clinical practice), which is focused on recommending them to seek psychological health care for further evaluation. MI efficacy will be compared to the current TAU as the control condition. The primary outcome is the utilisation rate of psychological health care after counselling by an MI-trained physician vs. an untrained physician. Additionally, reasons for not claiming psychological support and changes in disease-related parameters will be evaluated in a 6-month follow-up session.

**Discussion:**

This trial will evaluate the feasibility of MI as a way to improve the utilisation of mental health-care services by adolescents who need further support other than that provided by standard care for chronic diseases. Physicians offering MI to adolescents may serve as a model for optimising health-care management in daily clinical practice, which may improve adolescents’ long-term well-being by improving adherence to medical treatment and preventing negative lifelong consequences into adulthood.

**Trial registration:**

German Trials Register (DRKS), DRKS00014043. Registered on 26 April 2018. Düsseldorf University study ID: 2017114504.

**Electronic supplementary material:**

The online version of this article (10.1186/s13063-018-2997-5) contains supplementary material, which is available to authorized users.

## Background

Adolescence is a challenging period with many health-related developmental tasks, risks and opportunities. Approximately 15% of German adolescents suffer from chronic medical conditions, such as asthma, diabetes and rheumatic diseases [1]. With these diseases, comorbid psychological symptoms, such as anxiety, depression and behavioural problems, are present in 10–40% of patients [2–6]. A complex interplay exists between anxiety and depression, disease attitude and treatment adherence. A screening measure for anxiety and depression has been introduced for some conditions, such as cystic fibrosis [2], but is not generally implemented for adolescents with other chronic diseases. In addition, no data exist on whether merely identifying anxiety or depression will result in improved mental health care. Furthermore, comorbid behavioural and emotional symptoms in adolescents with chronic conditions detrimentally affect medication adherence and adaption and increase the risk for negative long-term health outcomes [7]. Mental health issues are often neglected in current specialised medical care and physicians encounter substantial barriers in motivating adolescents to utilise psychological support [8]. Adolescents are highly resistant to considering psychological care for themselves [9]. Expert psychological interventions for coping with chronic conditions in the face of anxiety and depression have a robust evidence base [10, 11]; however, access to such services is only sporadic [12]. Referring adolescents to mental health care without appropriately motivating them often fails.

This study is part of the COACH trials consortium. COACH (Chronic Conditions in Adolescents: Implementation and Evaluation of Patient-centred Collaborative Health Care) is part of a nationwide research initiative to improve the mental health of children and adolescents, called *Gesund – ein Leben lang*, which is supported by the Federal Ministry of Education and Research, Germany. Consortium partners in Berlin, Potsdam, Ulm and Düsseldorf work together with different subprojects (such as motivational interviewing or MI in Düsseldorf). The steering committee is in Ulm. The aim of the COACH consortium is to demonstrate the efficacy of early behavioural interventions on health outcomes for adolescents with chronic medical conditions. First, the needs of adolescents with chronic medical conditions will be identified, and then the risk factors for comorbid mental health issues will be analysed. The long-term aim is to develop a model of collaborative care and pathways for disseminating and implementing early behavioural interventions into clinical practice.

The study on motivational interviewing (COACH-MI subproject) aims to determine the efficacy of an early intervention using MI for adolescents with chronic medical conditions to improve their utilisation of appropriate services, from paediatrics to mental health care, after early referrals for anxiety or depression.

MI is a collaborative evidence-based counselling technique designed to intrinsically motivate and strengthen patients’ commitment to improving a range of health behaviours [13–15]. MI has previously been shown to be effective in adolescent populations. It has been evaluated across different chronic medical conditions and positively affects the uptake of cognitive behavioural therapy (CBT) [16–22]. In the latter study [22], a clinical psychologist with postgraduate MI training conducted individual MI and active control (befriending) sessions with adolescents who had been diagnosed as having mood or anxiety disorders to improve treatment engagement in a standard therapy setting (group CBT). The new aspect of our study is that MI will be delivered by physicians treating patients with chronic conditions who have screened positive for anxiety and depression symptoms to decrease these adolescents’ unwillingness and concerns regarding psychological health care.

If the intervention is superior to treatment as usual (TAU), MI may be taught to and implemented by physicians in paediatric care, at least for those physicians who treat patients with chronic conditions. In the long term, stabilising mental conditions in adolescents through an early referral to mental health care could lead to better treatment adherence and self-management in chronic conditions, thus preventing long-term health consequences. Currently, physicians are often untrained in patient-centred communication with adolescents.

### Objectives

This study will determine the efficacy of providing adolescents with MI sessions administered by MI-trained physicians to improve mental health-care uptake rates. Patients who screen positive for anxiety or depressive symptoms will have two MI sessions with a trained physician or TAU (by a physician untrained in MI). We expect adolescents to benefit from conversations utilising the MI approach. The primary objective is to test whether MI increases the utilisation of supportive psychological counselling in patients with symptoms of anxiety or depression. For those individuals who do not seek psychological health care, we will analyse the reasons why the recommendations were not followed. Secondary outcomes, which will be measured at the 6-month follow-up, include improved symptoms of anxiety and depression and treatment-related parameters. Furthermore, treatment fidelity and the success of brief MI training sessions for physicians in our facility will be analysed by evaluating the interviews. The prevalence of anxiety and depressive symptoms will be analysed for a broad spectrum of chronic diseases.

### Study design

This study will be conducted as a pragmatic cluster-randomised monocentric controlled trial at the University Children’s Hospital Düsseldorf with two parallel groups (Fig. 1).

**Fig. 1 Fig1:**
[figure not shown]
Flow chart of study design. ITT intention to treat, MI motivational interviewing, TAU treatment as usual

## Methods/design

### Eligibility criteria

#### Inclusion criteria

Adolescents with chronic medical conditions will be eligible for mental health screening if they are between 12 and 20 years of age. Chronic medical conditions are diseases that persist for >1 year. They significantly impair the patient’s daily routine and require continuous care and/or medical treatment.

To achieve high external validity, we plan to screen all patients attending the outpatient department of the University Children’s Hospital, Düsseldorf, Germany, who fulfil the inclusion criteria, and we will randomise all physicians who oversee the medical care of these patients.

Patients who screen positive with depression or anxiety symptoms will be counselled by their treating physician, who will have previously been randomised to perform either MI or TAU.

#### Exclusion criteria

Participants will be excluded if they are currently attending regular psychotherapy at the time of recruitment, or those with psychosis, acute suicidality, severe intellectual disability (IQ < 70), inability to communicate (verbally or in writing) or who currently abuse alcohol or drugs.

### Study interventions

#### Screening

Anxiety and depression will be screened as part of the clinical routine. After providing informed consent, participants will complete the following screening questionnaires on a tablet computer in the outpatient clinic immediately prior to their scheduled appointment: the Generalised Anxiety Disorder 7-item scale (GAD-7) [23] and the depression portion of the Patient Health Questionnaire (PHQ-9) [24–26]. Patient-reported outcomes on disease-related parameters will be assessed after the standardised screening questionnaires (see below).

Immediate feedback will be provided based on the results of these screening tools. Positive screening, defined as either a GAD-7 or PHQ-9 score ≥ 7, will trigger a recommendation for supportive counselling (see Section 1.2). Negative screening results will be conveyed to the adolescent and a psychoeducational handout will be provided.

#### Training of the treating physicians in motivational interviewing

As a prerequisite, physicians randomised to the MI group will attend a 2-day MI training course certified by the Motivational Interviewing Network of Trainers. Their ability to practise MI will be evaluated based on recorded counselling sessions in a standard procedure known as the motivational interviewing treatment integrity check. The results will be delivered to and discussed with the physician to improve their MI skills. A 2-day course in MI has been shown to provide sufficient and successful training to clinicians [27].

Patients being treated by MI physicians who screen positive will be provided with two counselling sessions implementing MI. The first MI session will be conducted immediately after the screening and will last 15–50 min. Sessions will be audio-recorded after mutual agreement. A second appointment will be scheduled within 2–4 weeks for a second 30–50 min MI session. MI aims to engage the patient in discussing the option for professional psychological support, focusing on their thoughts when considering this option and discussing possible barriers as well as pros and cons. This technique will be used to consider change as an option and to change their behaviour, i.e. to meet with a psychotherapist or other health-care provider delivering psychological treatment or psychotherapy in our facility.

#### Treatment as usual

The control condition is TAU, which includes providing immediate advice after the screening to seek psychological support. The physician will inform the patient of the assumed need for mental health care based on the screening questionnaire results, without specifically considering the adolescent’s perspective or potential barriers to the adolescent using this recommended support. The TAU physicians will perform their usual standard of care. They are free to deliver their counselling with no requirements regarding time span, content or conversation techniques. The duration and content of the conversation after a positive screening result will be briefly documented by the physicians.

The study physicians in both groups will provide a standardised written recommendation for the patient to seek specialised mental health counselling, specifically by psychotherapists. The document contains the addresses of local offices that can schedule psychological or mental health care appointments.

Both MI and TAU conversations will be audio-recorded for qualitative and quantitative analyses by mutual consent.

### Outcomes

#### Primary outcome

The primary outcome is the utilisation of psychological health care. All patients with positive screening results are recommended to seek psychological counselling or psychotherapy. Successful referral is any appointment for psychological health care, defined as counselling with a (child and adolescent) psychotherapist, psychologist, psychiatrist or internet-based CBT counsellor in at least one face-to-face or digitally delivered session of psychological treatment within the 6-month follow-up interval. Patients on waiting lists (for psychological health-care appointments) will be counted as a positive outcome and will be reported separately. The primary outcome will be assessed via a semi-structured interview (telephone or face-to-face during a follow-up visit, Fig. 2) by blinded independent assessors unaware of the patient’s allocation.

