#### Secondary outcomes

The secondary outcomes include baseline changes in anxiety and depression scores (GAD-7 and PHQ-9), disease-related parameters and the number of sessions attended by the follow-up. The follow-up interview will gather concrete data on the counsellor thereby enabling us to evaluate which form of psychological support (psychotherapy, counselling, psychiatric treatment or internet-based CBT) was used or to identify patients’ reasons for not using psychological health care.

Besides anthropometric data (age, gender, height, weight, body mass index and disease duration), the following disease-related parameters will be assessed: the need for technical aids (e.g. a wheelchair or oxygen), daily treatment duration, global assessments of limitations in daily life and pain, days absent from school or work, missed clinical visits and adherence measures using the Medication Adherence Rating Scale, German version (MARS-D) [28]. For diabetes (HbA1c), lung diseases (FEV1 expected) and juvenile idiopathic arthritis (Juvenile Arthritis Disease Activity Score) disease-specific parameters will be assessed. We will examine possible serious adverse events (SAEs) associated with the present screening and MI education approach. Gender-specific results will be analysed.

Audio-recorded MI/TAU conversations will also be quantitatively and qualitatively analysed using standardised tools (e.g. the motivational interviewing treatment integrity check) to assess treatment fidelity.

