#### Sample size

The proposed sample size for the baseline mental health screening assessment in our monocentric study is estimated at approximately *n* = 1,000 cases in 24 months. The prevalence of depression or anxiety symptoms is estimated at 15–20% in total across the disease spectrum [2] (Fig. 1).

The rate of successful mental health-care referrals for TAU is estimated at 10% [40] and we expect an increase to at least 30% for the intervention group. For a two-sided chi-square test with a power of 80% and a significance level of 5%, the software NQuery 8.0 (Statistical Solutions, 2018, Cork, Ireland) gives a sample size of *n* = 62 per group. We will correct the sample size by 10% for cluster effects, resulting in an estimated intra-cluster correlation coefficient of 2.5% and a sample size of *n* = 69 per group. To adjust for a 15% drop-out rate, the sample size per group is targeted at *n* = 81, treated by either MI physicians or TAU physicians, for a total of *n* = 162 patients (Fig. 1). All cases included in the study will be analysed by an intention-to-treat analysis.

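### The primary outcome does not require that psychological care or a waiting-list place began after the study recommendation, and the entry criteria exclude only regular psychotherapy, so some pre-existing care can count as success

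*Protocol article*

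**What the plan says.** Under Exclusion criteria, the only rule on existing mental health care is: "Participants will be excluded if they are currently attending regular psychotherapy at the time of recruitment". The other exclusions concern psychosis, acute suicidality, intellectual disability, inability to communicate, and substance abuse.

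Under Primary outcome, success is wider: "Successful referral is any appointment for psychological health care, defined as counselling with a (child and adolescent) psychotherapist, psychologist, psychiatrist or internet-based CBT counsellor". The sentence goes on: "in at least one face-to-face or digitally delivered session of psychological treatment within the 6-month follow-up interval". A further rule adds: "Patients on waiting lists (for psychological health-care appointments) will be counted as a positive outcome and will be reported separately".

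Under Secondary outcomes, the follow-up interview is to establish "which form of psychological support (psychotherapy, counselling, psychiatric treatment or internet-based CBT) was used". The protocol thus treats psychotherapy as one of four forms of support.

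Under Sample size, the planning rates are "The rate of successful mental health-care referrals for TAU is estimated at 10" per cent and "we expect an increase to at least 30% for the intervention group". The calculation gives 62 per group, then 69 after the cluster correction and 81 after allowance for drop-out.

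**The concern.** The primary objective is whether MI increases uptake of psychological support. Someone already receiving countable care, or already waiting for it, cannot show that change, yet the definition as written scores that person as a success. The exclusion closes this gap only for regular psychotherapy, while the outcome covers four provider types and waiting lists.

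Two things follow. If prior care is equally common in both arms, these patients raise both success rates and shrink the contrast, which costs power. If it happens to differ between the physicians allocated to MI and to TAU, the difference enters the observed effect as noise. Physicians from seven specialised departments are the randomised units, so patients with prior care need not be spread evenly. The exploratory model gives age, sex and medical condition as example covariates; prior care is not among them.

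**Working it through.** **Comparing entry rule and outcome, by state at screening**

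| State at screening | Excluded at entry? | Can count as success? |
|---|---|---|
| Regular psychotherapy | Yes | Not applicable |
| Irregular psychotherapy | No | Yes, one session in 6 months |
| Occasional counselling with a psychologist | No | Yes, if a session of psychological treatment |
| Internet-based CBT | Not clearly | Yes, one digital session |
| Psychiatric follow-up | No | Only if a session is psychological treatment; a medication-only visit may not be |
| First appointment already booked | No | Yes, once attended |
| Already on a waiting list | No | Yes, if still waiting or seen by month 6 |

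The waiting-list row is the clearest. The patient is not attending psychotherapy, so passes entry, and the waiting-list rule does not ask when the patient joined.

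**Reproducing the plan's sample size**

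Inputs from Sample size: p0 = 0.10, p1 = 0.30, two-sided 5%, power 80%. With p̄ = (p0 + p1)/2,

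n = [1.96·√(2p̄(1−p̄)) + 0.842·√(p0(1−p0) + p1(1−p1))]² / (p1−p0)²

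= [1.96 × 0.5657 + 0.842 × 0.5477]² / 0.04 = 61.6, so 62.

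Then 62/0.9 = 68.9, so 69; and 69/0.85 = 81.2, stated as 81. The plan's figures reproduce, and power at 62 is 80.3%.

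**Adding prior users**

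Let f be the share of screen-positive patients already in countable care, booked or wait-listed. The documents do not give f; 5% to 20% is an assumed range. Assume also that 10% and 30% are the rates among the others, and that every prior user is a success. Then

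rate in an arm = f + (1−f)·p

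power = Φ{[(p1−p0)·√62 − 1.96·√(2p̄(1−p̄))] / √(p0(1−p0) + p1(1−p1))}

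At f = 10%: 0.10 + 0.90 × 0.10 = 0.19 and 0.10 + 0.90 × 0.30 = 0.37. Power = Φ[(0.18 × 7.874 − 1.96 × 0.6350)/0.6221] = Φ(0.278) = 61%.

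| f | TAU | MI | Difference | Odds ratio | Power at 62 | n per group before inflation | n per group after both inflations |
|---|---|---|---|---|---|---|---|
| 0 | 10% | 30% | 20 points | 3.9 | 80% | 62 | 81 |
| 5% | 14.5% | 33.5% | 19 points | 3.0 | 70% | 79 | 104 |
| 10% | 19% | 37% | 18 points | 2.5 | 61% | 97 | 128 |
| 20% | 28% | 44% | 16 points | 2.0 | 46% | 141 | 185 |

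Most of the loss at small f comes from the larger variance at higher rates, not from the smaller difference.

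**If prior users are not certain successes**

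Suppose only half of them have a countable event in either arm. At f = 10% the rates are 0.05 + 0.09 = 14% and 0.05 + 0.27 = 32%, with power Φ[(0.18 × 7.874 − 1.96 × 0.5951)/0.5814] = Φ(0.431) = 67%, against 61% above. So, with 10% and 30% as rates in non-users, the table shows the largest loss for each f.

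**Imbalance (illustration, shares assumed)**

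With f = 5% in TAU, 15% in MI and no MI effect, the expected rates are 0.05 + 0.95 × 0.10 = 14.5% and 0.15 + 0.85 × 0.10 = 23.5%, a gap of 9 points produced by prior care alone. The opposite split is equally possible under randomisation.

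**The case against.** The best counter-argument is that the definition opens with the label of a successful referral and follows directly on the statement that screen-positive patients are advised to seek care. A sensible assessor might count only what came after that advice. This shows the intent. But the operative words that follow set only provider, number of sessions and window, and the waiting-list rule sets no start date, so a blinded assessor who follows the text would count existing care.

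Several stronger readings should be resisted:

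- **Any contact with a psychiatrist or psychologist counts.** It does not: a session of psychological treatment is required, so routine psychiatric or medication review need not qualify.
- **Patients with prior care are to be expected in number.** The documents do not say so. The Background describes neglected mental health needs, reluctant adolescents and sporadic access, and regular psychotherapy is already excluded. f may be small.
- **The planned contrast of 10% against 30% becomes unattainable.** At f = 5% the difference is still 19 points, and the plan expects at least 30%. The 10% comes from a cited source and may already include some prior users, in which case the loss would differ from the table.
- **The primary effect is biased by imbalance.** Chance imbalance between randomised clusters is random error, which the mixed model is meant to reflect. The allocation method may also balance by department, though its description is unclear.
- **Prior care is never asked about.** The schedule of assessments is a figure that is not shown, and this is a journal article. Applying the exclusion already requires a question on current therapy, and follow-up records sessions in detail. A baseline item may exist, but the outcome definition makes no use of one.

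These points limit the size of the problem and the confidence in it. They do not remove the mismatch.

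**Conclusion.** The concern holds in a limited form. As written, the primary outcome can credit MI or TAU with care, bookings or waiting-list places that predate the recommendation, because the exclusion is narrower than the outcome. With balanced prior care the result is dilution towards no difference; with chance imbalance it is added noise in either direction.

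The size cannot be fixed from the document. A fall in power from 80% to 70%, 61% or 46% rests on assumed f of 5%, 10% or 20%, on 10% and 30% being rates among non-users, and on all prior users being successes. The point should be fixed, since it concerns the primary outcome and the repair is cheap. It does not show that the trial will fail or that its result will be systematically biased. Confidence is moderate.

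**What to change.** 1. At baseline, record any current, arranged or wait-listed psychological care, using the same provider list as the outcome, if the full protocol does not already do so.
2. In Primary outcome, define success as a session of psychological treatment, or a waiting-list entry, newly started or arranged after the first study session.
3. Add a sensitivity analysis that excludes patients with any such care at baseline.

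With this definition the planning rates can again be read as rates of new uptake, and 62, 69 and 81 per group can stand.

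The cost is one baseline question and one sentence in the definition. Reported utilisation rates will be slightly lower. A patient who moves from sporadic contact to fuller treatment with the same provider would not count as new uptake, so such intensification should be reported separately. Widening the exclusion instead would also close the gap, but it would lose some screen-positive patients and narrow a trial that aims at high external validity.
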